## Abstract

**Background:**

Attention deficit/hyperactivity disorder (ADHD) has a negative impact on several domains of life. However, there is a shortage of evidence-based non-pharmacological treatments for adolescents with ADHD. A structured skills training group (SSTG) based on dialectical behaviour therapy (DBT) has been used in adult patients with ADHD with some promising results, although the treatment has not yet been adapted or evaluated for adolescents with ADHD. This study protocol describes how this treatment was adapted for an adolescent population and how the efficacy of the SSTG will be evaluated using a randomised controlled trial (RCT) design.

**Methods:**

A sample of 184 adolescents (15–18 years of age) with a diagnosis of ADHD has been recruited from seven child and adolescent psychiatric outpatient units and randomised to either the SSTG or an active control group based on psychoeducation. Measures are conducted weekly during the treatment, as well as 2 weeks before treatment and 2 weeks and 6 months after treatment. The primary outcome measures are ADHD symptoms, functional impairment, quality of life and mindfulness. Secondary outcome measures are symptoms of comorbid psychopathology, perceived stress and sleep problems. This article describes the design, methods and analysis plan for evaluating the efficacy of the SSTG.

**Discussion:**

The study will be the first RCT to examine the acceptability and efficacy of a SSTG based on DBT adapted for adolescents with ADHD. We believe that the study will extend the current knowledge base about psychological treatment for adolescents with ADHD.

**Trial registration:**

ISRCTN registry (ISRCTN17366720). Retrospectively registered May 112,016.

**Electronic supplementary material:**

The online version of this article (10.1186/s12888-019-2133-4) contains supplementary material, which is available to authorized users.

## Background

The presentation of attention deficit/hyperactivity disorder (ADHD) changes across the life span, with younger children displaying more hyperactivity-impulsive behaviours and adolescents and adults exhibiting more symptoms of inattention [1]. During adolescence, emotional lability and substance use become a growing problem, as well as comorbid mood and anxiety disorders [1]. In addition, academic, interpersonal and social problems become more pronounced during this period of life [2–4].

Given the negative impact of ADHD throughout the lifespan, it is imperative to implement treatments that are acceptable and effective for patients of different ages. For children and adolescents, non-pharmacological interventions such as psychoeducation are regarded as the first-line treatment; however, in moderate to severe cases of ADHD a combination of pharmacological and psychosocial treatment is recommended [5, 6]. Most studies on psychosocial treatment for younger age groups with ADHD have included children or parents to children and only a paucity of studies have included adolescents with ADHD [7]. However, because adolescence is a period marked by rapid developmental changes with an increased desire for independence and autonomy [8], it is not evident that treatment methods directed towards children are equally feasible and effective for adolescents. Moreover, compared with children and adults with ADHD, adolescents are more likely to discontinue pharmacological treatment [9] which further underscores the need to develop non-pharmacological treatment options for this group.

Cognitive behavioural therapy (CBT) has proven to be effective in treating children and adolescents with different psychiatric problems, e.g., anxiety and depression [10, 11]. CBT is generally characterised by using concrete goals and individual problem analyses, with focus on how emotions, thoughts and behaviours interrelate within a certain context [12]. A few CBT studies have been conducted in adolescents with ADHD, both delivered individually [13, 14] and in a group setting [15]. Preliminary findings indicate that CBT could be an effective treatment for some adolescents with ADHD, even though more studies are needed to draw any definitive conclusions.

As a further development of CBT, dialectical behaviour therapy (DBT) was originally developed for patients with borderline personality disorder (BPD) and suicidal ideation [16] to specifically target management of interpersonal relations and emotion dysregulation. Within DBT, a strive for balance between change and acceptance within a dialectical framework is emphasised, and techniques such as mindfulness, behavioural analysis, social skills and crises management are continuously practiced in the treatment [17]. There is symptom overlap between ADHD and BPD with difficulties in emotional regulation, impulse control, interpersonal relations, substance abuse and poor self-esteem [18]. Given this overlap in symptoms, a structured skills training group (SSTG) with elements of DBT (as well as CBT) has been developed for adult patients with ADHD [19]. The treatment has thus far yielded mixed results. Using an open study design, the treatment has been associated with a reduction in ADHD symptoms, functional impairment, symptoms of comorbidity and improvement in personal health [19–21]. However, when using a RCT design, a reduction in ADHD symptoms, but not in symptoms of comorbidity, have been reported when compared with a loosely structured discussion group [22]. In the largest RCT performed, only the blinded clinical global impression ratings supported SSTG to be superior to an individual clinical management [23]. These mixed findings highlight the importance of the RCT study design. Current recommendations for first-line treatments for ADHD includes psycho-educative interventions [6]. Therefore, psychoeducation is an appropriate control intervention for future RCT studies.

Although SSTG has not yet been adapted or evaluated regarding its efficacy for adolescents with ADHD, a small pilot study of seven adolescents with ADHD concluded that the treatment was feasible and appreciated by the participants but that the manual needed to be age-adjusted to be more optimal for adolescents [24]. To increase the prerequisite for adolescents to be engaged in and benefit from treatments originally developed for adults it is necessary that the participants understand, perceive and relate to the content. Therefore, adaptations in the language, materials, examples and activities need to be tailored to fit the age group [17, 25]. These adaptations may include the use of visual material [26] to clarify the content, as well as more active and experiential exercises (e.g., role play, discussions and practising skills) to increase engagement [17, 27]. An active approach is likely to be especially important in working with adolescents with ADHD who have difficulties maintaining concentration in teaching situations.

## Aims

The study aims to investigate the efficacy of an age-adapted SSTG based on DBT for adolescents with ADHD in a clinical setting using an RCT design with an active control group based on psychoeducation. The study also aims to investigate whether subgroups (e.g., based on subtype of ADHD and symptoms of comorbidity) respond differently to the treatment, and finally, whether the SSTG is acceptable to adolescents with ADHD. We hypothesise that (i) the SSTG will result in a greater reduction of ADHD symptoms and functional impairment, and an increase in mindfulness and quality of life, than a psychoeducational group treatment, and (ii) the SSTG will lead to a greater reduction of symptoms of comorbidity, perceived stress and sleep problems compared with the psychoeducational group treatment.

## Methods/design

### Study design

The study design is a multicentre RCT with two treatment conditions: 1) A SSTG based on DBT and 2) a psychoeducational group treatment. Participants are randomised to either one of the two manualised interventions, both tailored to be used for adolescents with ADHD and delivered via the local child and adolescent psychiatric outpatient units. The study is planned in accordance with the Standard Protocol Items: Recommendations for Interventional Trials (SPIRIT) 2013 [28], and will be analysed and reported in accordance with the recommendations in consolidated standards of reporting trials (CONSORT) [29]. We strive for transparency and any changes and deviations from the protocol will be reported.

### Participants and procedures

Recruitment, treatment and data collection are conducted in seven cities in Sweden (Gävle, Falun, Karlstad, Uppsala, Uddevalla, Västerås and Växjö Additional file 1), beginning in 2015, with the last post-treatment measurement expected to be finalised in the spring of 2019. Adolescents (15–18 years of age) from the local child and adolescent psychiatric (CAP) outpatient units with a known diagnosis of ADHD have been informed about the study through flyers in waiting rooms, verbally by the clinical staff, or both. For those who have shown interest, more information has been provided at an extra meeting and the staff have evaluated the patients’ eligibility for the study (see below). Before final inclusion, participants and their parents provided written informed consent. Study participation is voluntary and can be interrupted by the participant at any time. Eligible patients have then been randomised to one of the two treatment conditions. Adolescent self-reports and parental ratings have been collected 2 weeks before the start of the treatment, during the treatment, and are continuously collected 2 weeks and 6 months after conclusion of the treatment. Pre- and post-treatment instruments are administered using an online platform to which only the research group has access and coded data is stored in a secure server. The participating parents are continuously reminded by the research team to complete the questionnaires. When both the adolescent and their parent have completed the last measurement, they will receive two cinema tickets. Initially, the plan was to continue the recruitment until at least 100 patients had completed treatment. In total, 184 patients have been randomised. Of these, 159 adolescents and 162 parents have completed baseline assessments and the last post-treatment evaluations are now continuously being collected (Fig. 1). Those who were randomised but never underwent a baseline assessment were considered external dropouts. Those who completed the baseline assessment, but did not complete the treatment, will be considered internal dropouts.

**Fig. 1 Fig1:**
[figure not shown]
Study flow chart

### Eligibility criteria

To participate in the study the adolescents had to be 15–18 years old, be a patient at one of the designated CAP units and have a diagnosis of ADHD/ADD or ADHD-not otherwise specified according to ICD-10. The diagnosis is validated by using the section for ADHD in the Mini International Neuropsychiatric Interview for Children and Adolescents (MINI-KID) [30]. The assessment was performed by clinical psychologists who were trained in MINI-KID and who also assessed the participants’ eligibility for the inclusion and exclusion criteria. Adolescents were excluded if they showed symptoms of severe depression, suicidality, psychosis or bipolar disorder without a stable medication, a diagnosis of mental retardation, diagnosed organic brain injury, autism spectrum disorder or ongoing substance abuse. Ongoing pharmacological treatment had to be stable and the participants were asked not to change medication during the period of treatment. In addition, the clinical staff were also informed not to change medication or medication dose during the treatment period. Nevertheless, patients will not be excluded if their medication were changed during the treatment period; instead, any changes in medication will be adjusted for in the analyses. The participants were requested not to participate in any other psychological treatment during the treatment period and the parents were requested not to participate in any parent educational programme during this period. The treatment took place at the adolescents’ CAP units and any deterioration of symptoms during the treatment are handled by the units. Any negative reaction could be discussed with the supervisor. Since the treatment is given as part of the regular health care, the patients are covered by the patient injury insurance.

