### Trial arms

#### Structured skills training group (SSTG)

The treatment is an age-adjusted version of a manualised DBT-based group programme originally developed in Germany for adults with ADHD [19, 31] and later translated and evaluated in a Swedish population [22, 32]. The SSTG consists of 14-weekly 2-h sessions. Each session has its own theme (Table 1), including discussions and exercises. The themes are presented to the participants in a workbook and through a PowerPoint presentation. Themes specific for DBT, such as mindfulness, acceptance and behavioural analysis, are continuously practised during the treatment sessions. Each group was led by two therapists, of which at least one was trained in DBT. All of the therapists are educated in the treatment and they discussed the manual in yearly meetings. A clinical psychologist, trained in both CBT and DBT, offered the therapists continuous supervision throughout the study. In addition, the therapists were instructed to video record the group sessions to enable assessment of manual adherence.

**Table 1 Tab1:** Description of the themes and content of the structured skills training group

Session	Themes
1.	*Introduction:* Introduction and overview of the treatment, psychoeducation about ADHD, strengths, and difficulties with ADHD and introduction of the main themes of treatment. Define goals. Give a home assignment, which is a central part of all sessions.
2.	*Neurobiology and mindfulness I:* Neurobiology of ADHD, emphasising difficulties in executive functions and the possibility to improve functions through practice, e.g. mindfulness training. Introducing mindfulness. Thereafter, mindfulness training is included in all sessions.
3.	*Homework and mindfulness II:* The purpose and importance of homework as a part of the treatment are emphasised. Participants receive tips for how to get the home assignments done.
4.	*Acceptance and mindfulness III*: The balance between acceptance and change is discussed. The concept of “wise mind” and the integration of the emotional mind and the reasonable mind is introduced.
5.	*Chaos and control:* Difficulties in organization and planning are highlighted and strategies with the aim to increase control are introduced.

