6	*Emotions:* Education in emotion theory (primary emotions, connection between emotions, thoughts, behaviours, signals and communicatory aspects of emotions, emotions and ADHD). Practice in identifying, observing, and describing emotional signals to regulate and cope with emotions.
7–8.	*Behavioural analysis:* Participants are introduced to behavioural analysis (preceding events/internal and external “triggers”, behavioural responses, and consequences). Strategies to find alternative behaviours are introduced and practiced. Behavioural analysis is applied on own examples and thereafter used throughout treatment.
9.	*Medication, mental illness, and how to increase wellbeing:* Information and discussion about pharmacological treatment for ADHD, documented effects as well as side effects. Symptoms of depression and other emotional problems are discussed, also focusing on treatment, preventive strategies, and emotional regulation.
10.	*Impulsivity, risk behaviour, and addiction:* Symptoms of addiction and other forms of risky behaviours are discussed. Practice in identifying, describing, and regulating impulsive behaviours using mindfulness and behaviour analysis as strategies.
11.	*Stress:* Physiological reactions of stress and the relation between stress and performance are covered. Exercises in identifying and learning about own personal stress are performed. Strategies for stress management are taught.
12–13.	*Self-esteem and relationships:* Differences between self-esteem, self-confidence, and self-respect are clarified, including the impact of ADHD on these areas. Social skills are taught and practiced.
14.	*Retrospect and outlook:* The participants summarize their experience of the group treatment, identify achieved, as well as remaining goals and plan for maintaining progress and how to manage future problems.

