##### Other measurements

Before and after treatment, parents are asked to report the adolescents’ current medication and dose of medication. During the treatment, the group leaders registered attendance and completed home assignments. During the final session, the adolescents completed an evaluation form specifically constructed for this study to assess the acceptability of the treatment. The evaluation form includes questions on how the participants perceived and responded to the treatment, the content and length of the treatment and if they would recommend the treatment to their peers.

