### Statistical methods

#### Statistical analysis plan

The treatments were finalised during 2018 while post-treatment ratings are currently being collected. Analysis of the data will start in the summer of 2019. The statistical analysis will be conducted on all participants who completed the pre- treatment (baseline) questionnaires (*n* = 159 adolescents and *n* = 162 parents). Missing post-baseline data for any of the participants because of the absence of any session or dropout will be handled by multiple imputations using last mean carried forward (LMCF) [47]. A sensitivity analysis will be performed for those who completed the treatments (e.g., attended at least two thirds of the sessions) without using LMCF. Primary and secondary outcome variables will be analysed with repeated measurements in general linear models using the baseline value for respective outcome as a covariate. The primary analysis will be aimed at investigating differences between the two treatment groups in reduction in ADHD symptoms and functional impairment, and increase in mindfulness and quality of life, directly and 6 months post-treatment. Secondary analyses will be aimed at investigating the group treatment effects on reported symptoms of comorbid psychopathology and health-related status. Moreover, the two treatment groups will be compared for treatment acceptability. As separate analyses, we intend to explore any difference in outcome measures based on subgroups of clinical relevance (e.g., subtype of ADHD and symptoms of other psychopathology). We also plan to validate and investigate the psychometric properties of the newly developed questionnaire, IAS, which was constructed to assess the impact of ADHD symptoms on the adolescents’ wellbeing during the treatment intervention. Guidelines for the specific rating scale will be used in the choice of imputation of missing data within the scales. If no guidelines are available, an imputation of the mean of the subscale for that specific participant will be used when less than 20% of the items are missing.

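### Adjusting for medication changes made after randomisation can move the result away from the effect of offering SSTG; the primary comparison should not do it

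*Protocol article*

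**What the plan says.** All references are to the protocol article.

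- **Eligibility criteria.** Medication had to be stable, participants were asked to leave it unchanged, and "the clinical staff were also informed not to change medication or medication dose during the treatment period". Even so, a patient whose drug or dose is altered while treatment runs stays in the trial. On how the analysis deals with this, the section states: "instead, any changes in medication will be adjusted for in the analyses". The sentence does not say which analyses it covers, and it does not confine the adjustment to a sensitivity analysis. The same section says that "any deterioration of symptoms during the treatment are handled by the units".
- **Table 1, session 9 (SSTG).** The content includes "Information and discussion about pharmacological treatment for ADHD, documented effects as well as side effects". Table 2, for the control programme, lists no medication theme.
- **Trial arms.** "The SSTG consists of 14-weekly 2-h sessions"; the control treatment has three sessions, with no spacing given.
- **Other measurements.** "Before and after treatment, parents are asked to report"; the items reported are the drug in use and its dose. No date of change is mentioned.
- **Statistical analysis plan.** Outcomes are analysed with repeated-measures general linear models "using the baseline value for respective outcome as a covariate". Medication is not mentioned there.

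**The concern.** Randomisation balances what exists at baseline. A medication change during treatment comes later and may itself depend on the arm. The article shows three routes:

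1. **Directly.** Only SSTG has a listed session on medication, and allocation was open to participants.
2. **Through symptoms.** The trial expects SSTG to reduce symptoms more, and worsening is managed by the units, so the need for a change may differ by arm.
3. **Through time.** The interval between the two medication reports is probably longer in SSTG.

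If any route operates, conditioning on the change can do two things. It can take out the part of the SSTG effect that runs through medication. Where changes also follow prognosis, it compares patients in the two arms who reached the same medication status for different reasons, and so mixes prognosis into the contrast. The result is then not the effect of offering SSTG and not a clean effect in the absence of medication change. Because the sentence is unqualified, it can be read as governing the primary treatment contrast.

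**Working it through.** **The plan's own figure.** Sample size section: ASRS-A difference 7, SD 12, so d = 7/12 = 0.583; CSDS 4/7 = 0.571. With two-sided α = 0.05 and power 0.80, a two-sample t calculation gives 48 per group for ASRS-A, 50 for CSDS and 50 for d = 0.57. The stated figure of about 50 reproduces and does not depend on this point. It supplies the scale: a planned difference of 7 points and an SD of 12.

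**Everything below rests on assumptions**, because the article gives no rate or effect of medication change. Negative values favour SSTG.

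**1. Change depends on arm but not on prognosis.** Total effect = direct effect + medication effect × difference in change rates.
- Direct −5, medication effect −8, rates 35% and 17%: −5 + (−8 × 0.18) = −6.44. Simulation gave −6.48 unadjusted and −4.99 adjusted, a gap of 1.49 points (1.49/12 = 0.12 SD). Adjustment here recovers the direct effect of −5, so the gap is the distance between two estimands.
- Rates 10% and 5%, same medication effect: 8 × 0.05 = 0.40 points (0.40/12 = 0.03 SD).

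**2. Change also depends on prognosis.** The model has arm A (0/1), prognosis U and noise e (both standard normal):
- logit P(change) = logit(p0) + k(0.7U + τA/12) + gA
- Y = τA + 12(0.7U + √(1 − 0.49) e) + mM, where M = 1 if medication changed

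The unadjusted arm difference is compared with the arm coefficient when M is in the model (2,000,000 records per row; shifts taken before rounding).

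| τ | p0 | k | m | odds ratio, arm on change | change rate SSTG / control | unadjusted | adjusted | shift |
|---|---|---|---|---|---|---|---|---|
| −7 | 5% | 0 | 0 | 1 | 5.0% / 5.0% | −6.98 | −6.98 | 0.00 |
| −7 | 5% | 1 | −5 | 1 | 3.5% / 6.1% | −6.88 | −6.86 | +0.02 |
| −7 | 5% | 2 | 0 | 1 | 3.6% / 9.4% | −7.00 | −6.41 | +0.58 |
| −7 | 20% | 2 | 0 | 1 | 12.6% / 26.5% | −7.01 | −5.74 | +1.27 |
| −7 | 30% | 2 | 0 | 1 | 18.1% / 34.9% | −7.00 | −5.51 | +1.49 |
| −7 | 20% | 1 | 0 | 2 | 23.9% / 22.1% | −6.99 | −7.09 | −0.10 |
| 0 | 20% | 2 | 0 | 2 | 37.6% / 26.3% | 0.02 | −0.97 | −0.99 |
| 0 | 20% | 2 | −5 | 1 | 26.4% / 26.4% | −0.01 | −0.01 | 0.00 |

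If SSTG lowers symptoms and so lowers the rate of change, adjustment pulls the estimate towards zero. If SSTG itself prompts changes and has no effect on the outcome, adjustment produces an apparent benefit of about 1 point. If change is unrelated to arm, nothing moves, even when it depends on prognosis (last row). A separate run in which changes followed mid-course worsening and had no effect moved −7.01 to −6.75, a shift of 0.26 points (0.02 SD).

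These runs leave out the baseline covariate. In the planned model it would be expected to absorb part of the prognosis, so the prognosis-driven shifts may be smaller.

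**3. Treatment window.** Fourteen weekly sessions span 13 weeks; with measurement 2 weeks before and 2 weeks after, 13 + 4 = 17 weeks. If the three control sessions are also weekly (assumed), 2 + 4 = 6 weeks. With one constant rate of change in both arms, 10% over 6 weeks (assumed) becomes 1 − 0.90^(17/6) = 26% over 17 weeks. Length alone could then tie the covariate to the arm.

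**The case against.** **Changes may be rare.** Participants and staff were asked not to change medication. This stands: it limits the likely size, and the 35% and 17% rates and the 8-point effect above are assumptions at the high end.

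**The 1.5-point figure in step 1 is not bias.** A reader might infer that adjustment costs SSTG 1.5 points of true effect. That scenario does not show this, because the adjusted value there equals the direct effect exactly. It shows that the question being answered has changed. Distortion of the direct effect itself needs changes that follow prognosis as well as arm.

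**Session 9 is a thin route.** It is described as information and discussion, not encouragement to change, and controls also received psychoeducation and a book on ADHD whose coverage of medication is unknown. The route is plausible, not shown.

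**The unequal window is inferred.** A reader might take it as fixed by design, but the control programme's calendar length is not stated. If the window is unequal, an as-observed comparison also includes changes that arise only from the longer programme. That is part of offering it, and the article already lists the difference in length as a limitation.

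**The analysis section has no medication term.** A reader might infer a contradiction with the eligibility section. The analysis section is a condensed account and does not say that the baseline value is the only covariate, so this is a matter to reconcile. What does not fall away is the stated commitment itself, which is unqualified and has no estimand to justify it.

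**Conclusion.** The point holds in conditional form. The article commits to adjusting for a post-randomisation variable that the arm may influence. If it does, the adjusted contrast is not the effect of offering SSTG. If changes also follow prognosis, it is not a clean no-change effect either.

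Size and direction cannot be computed from the documents. Under the assumed inputs the shift runs from 0 to about 1.5 ASRS-A points against a planned 7, in either direction. It is zero when change is unrelated to arm and shrinks as changes become rarer. A reader might infer that the primary result will certainly be biased; the documents do not support that, since they show neither that changes differ by arm nor that the adjusted model is the primary one.

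Severity is moderate. The unadjusted comparison is available at almost no cost, so there is little reason to accept the risk.

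**What to change.** 1. State that the primary comparison uses outcomes as observed regardless of medication change, with the baseline outcome as covariate and, optionally, parent-reported medication status before treatment.
2. Report medication changes by arm.
3. Label any analysis that accounts for medication change as supplementary and state its estimand. Limit it to the post-treatment ratings: medication is documented only before and after treatment, without a date of change, so ratings made during treatment cannot be placed before or after a change.
4. Reconcile the sentence under Eligibility criteria with the model under Statistical analysis plan, so that both name the same covariates.

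The cost is wording and minor analysis work. The sample size and the conduct of treatment are unaffected, and no new measurement is needed. According to the article, post-treatment ratings were still being collected and analysis had not begun, so the change could be fixed before outcomes are compared.
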